###### 2nd Step in the Pregnancy Episode Algorithm: Assignment of Start Dates

In the pregnancy episode algorithm time periods need to be defined for various elements in order to calculate pregnancy start date. In Table 2 below the following time periods for each outcome are defined:

- Maximum pregnancy term - amount of time to search back from the outcome for all pregnancy markers. This time period should be the longest possible gestation period for an outcome so as to capture early markers.
- Minimum pregnancy term - Shortest possible gestational period for each outcome.
- Number of days a 2^nd^ pregnancy is possible after the outcome – This time window indicates how many days after the outcome specified another pregnancy may be initiated.

All time windows were estimated from research specific to each outcome and validated by in-house clinical experts.

| **Table 2: Time windows in days necessary to calculate pregnancy episode start date** | | | |
| --- | --- | --- | --- |
| **Outcome** | **Maximum Pregnancy Term** | **Minimum Pregnancy Term** | **Days 2nd pregnancy possible after outcome** |
| **LB** | 301 | 161 | 28 |
| **SB** | 301 | 140 | 28 |
| **DELIV** | 301 | 140 | 28 |
| **TRO** | 112 | 42 | 14 |
| **ECT** | 84 | 42 | 14 |
| **AB** | 168 | 42 | 14 |
| **SA** | 133 | 28 | 14 |

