1. If AFP date-123 exists between (larger of maximum term allowed subtracted from outcome date or prior outcome date plus retry count) and minimum term allowed subtracted from outcome date then AFP date-123 becomes the pregnancy start date.
2. If there are more than one AFP records in the allowed time window, use the first so as to use the AFP date that is most likely the recommended date in clinical guidelines rather than a repeat test.

**Step 5:** Outcome specific estimates:

1. If at least one PREM (premature term pregnancy), POSTT (post term pregnancy) or FT (full term pregnancy) record exists between (larger of maximum term allowed subtracted from outcome date or prior outcome date plus retry count) and 30 days after outcome date then categorize pregnancy as PREM, POSTT or FT.
2. If combinations of PREM, POSTT, FT records exist in this time window, categorize pregnancy in this order: 1) PREM if present, 2) POSTT if present, 3) FT if present.
3. Based on Table 4, choose an outcome specific gestational age estimate based on outcome and term and subtract from outcome date to obtain a pregnancy start date. If prior outcome date plus retry count is greater than outcome date minus outcome specific gestational age estimate then pregnancy start date becomes prior outcome date plus retry count.

**Step 6**: Choose final pregnancy start date:

1. Choose the best pregnancy start date (first one assigned in steps 1-5).
2. If a PCONF (pregnancy confirmation), AGP (antenatal GP visit) or OTEST (other pregnancy test) category records exist between (larger of maximum term allowed subtracted from outcome date or prior outcome date plus retry count) and minimum term allowed subtracted from outcome date and is prior to the best start date as calculated in the prior 5 steps then the first found PCONF, AGP or OTEST becomes pregnancy start date.

Table 4 provides outcome specific gestational age estimates for all outcomes for premature, post and full term pregnancies. These outcome specific gestational age estimates were obtained from Hornbrook et al.[[1](#_ENREF_1)] and Margulis et al. and were validated by in-house clinical experts and should represent average gestational times for the outcomes and terms.

| **Table 4: Outcome Specific Gestational Age Estimates in Days** | | | | |
| --- | --- | --- | --- | --- |
| **Outcome** | **PreTerm** | **PostTerm** | **FullTerm** | **NoData** |
| **LB** | 245 | 285 | 280 | 280 |
| **SB** | 196 | 285 | 280 | 196 |

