| **DELIV** | 245 | 285 | 280 | 280 |
| **TRO** | 56 | 56 | 56 | 56 |
| **ECT** | 56 | 56 | 56 | 56 |
| **AB** | 70 | 70 | 70 | 70 |
| **SA** | 70 | 70 | 70 | 70 |

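### Step 5 does not tie preterm, post-term and full-term records to the delivery and always ranks preterm first, so a stray record can misdate a birth, by up to 35 days for a full-term live birth

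*Protocol*

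**What the plan says.** Under Pregnancy Episode Start Date Calculation, Step 5 applies only when Steps 1 to 4 give no date: "Choose the best pregnancy start date (first one assigned in steps 1-5").

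- **Item 1** assigns a term category if a PREM, POSTT or FT "record exists between (larger of maximum term allowed subtracted from outcome date or prior outcome date plus retry count) and 30 days after outcome date".
- **Item 2** settles conflicts by a fixed ranking: "categorize pregnancy in this order: 1) PREM if present, 2) POSTT if present, 3) FT if present". The date of the record plays no part.
- **Item 3** subtracts the Table 4 estimate from the outcome date. If the result falls before the prior outcome date plus the retry count, that later date is used instead.

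Table 4 gives, in days for preterm, post-term, full term and no data: "LB | 245 | 285 | 280 | 280", "SB | 196 | 285 | 280 | 196" and "DELIV | 245 | 285 | 280 | 280".

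Table 2 sets the maximum term for these three outcomes at 301 days and describes it as the span to search for all markers, long enough to catch early ones. Its last column is 28 days for these outcomes: "This time window indicates how many days after the outcome specified another pregnancy may be initiated".

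Step 6 item 2 can then move the start earlier. For a PCONF, AGP or OTEST record inside the search window, the rule reads: "is prior to the best start date as calculated in the prior 5 steps then the first found PCONF, AGP or OTEST becomes pregnancy start".

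**The concern.** PREM, POSTT and FT state how long a pregnancy had lasted when it ended. A record made many months before a delivery cannot normally describe that delivery's term. Item 1 nevertheless searches the whole early-marker look-back, and item 2 lets one PREM record anywhere in it outrank an FT code entered on the delivery date.

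The start date is one of the quantities that the study sets out to get right, and the distribution of pregnancy terms by outcome is a planned output. The route is not rare in claims data. For Optum live births, Step 1 of the calculation says that LMP is absent and Step 2 gives GEST in 1.4%; Table 3 gives AFP in one third and nuchal ultrasound in 16%. Even with no overlap this is 1.4 + 33.3 + 16 = 50.7%, so at least about 49% reach Step 5. Only those with a stray term record are affected.

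**Working it through.** **Inputs.** Maximum term 301 and retry interval 28 days for LB, SB and DELIV (Table 2); Table 4 estimates; Step 5 items 1 to 3; Step 6 item 2. The Protocol does not define the retry count under that name; it is taken to be Table 2's last column. There is no stated figure to reproduce.

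**1. Window.** Put the current birth at day 0 and the prior valid birth P days earlier. The window runs from max(-301, -P + 28) to +30.

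**2. Records that precede the start they create.** A PREM record sets an LB or DELIV start at -245. Records from -301 to -246 precede it: 301 - 246 + 1 = 56 days. For SB the start is -196, so -301 to -197 precede it: 105 days. The floor shortens these spans when a prior birth is less than 329 days earlier.

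**3. What the floor keeps out.** The earliest admitted record lies max(28, P - 301) days after the prior valid birth.

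| P (days) | Earliest admitted record, days after the prior birth |
| --- | --- |
| 182 to 329 | 28 |
| 365 | 64 |
| 400 | 99 |
| 545 | 244 |
| 730 | 429 |

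So nothing dated up to day 27 after a valid prior birth enters, but later-coded records can. A birth's own window runs to day 30 and the next can open at day 28, so days 28 to 30 can count for both, for P up to 331. If the earlier pregnancy has no valid outcome, the 28-day floor drops out and the lag is only P - 301, for example 308 - 301 = 7 days.

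**4. Size of the shift.**

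| Outcome | Stray record | Own record | Shift of start |
| --- | --- | --- | --- |
| LB, DELIV | PREM | FT or none | 280 - 245 = 35 days later |
| LB, DELIV | PREM | POSTT | 285 - 245 = 40 days later |
| SB | PREM | FT | 280 - 196 = 84 days later |
| SB | PREM | none | 196 - 196 = 0 |
| SB | FT | none | 280 - 196 = 84 days earlier |
| SB | POSTT | none | 285 - 196 = 89 days earlier |

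TRO, ECT, AB and SA have one estimate each, so their shift is 0.

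**5. Effect of item 3.** For LB, the FT start is max(-280, -P + 28) and the PREM start max(-245, -P + 28). The difference is 0 for P up to 273, P - 273 for P from 274 to 307 (1 to 34 days), and the full 35 from P = 280 + 28 = 308.

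**6. Example.** Preterm live birth on day 0, a PREM record on day 30, and a live birth with an FT code on day 320. The spacing exceeds Table 1's 182 days. The window opens at max(320 - 301, 0 + 28) = day 28, so the day-30 record is admitted and PREM wins. The start becomes 320 - 245 = day 75; the FT code would give 320 - 280 = day 40. The error is 35 days, and the deciding record predates both starts.

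**7. Step 6.** In a 280-day pregnancy, a qualifying marker undoes the error, in part or in full, only if dated more than 245 days before birth, that is, in the first 280 - 245 = 35 days.

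**The case against.** The strongest reply is that the window already has a guard. The floor is the larger of two dates, and at ordinary birth spacings only very late records of the earlier birth pass it: 429 days or more after it at a two-year spacing. The day 28 to 30 overlap gives the full 35 days only for spacings of 308 to 331 days, and the example sits in that band. Steps 1 to 4 date many births first; in CPRD, Steps 1 and 2 put LMP or GEST in about 50 + 28 = 78% of live births. Step 6 repairs some of the rest. The PREM code list is not shown, and nothing says that follow-up of a preterm infant is coded to the mother. Ranking PREM first is also defensible for LB, where FT and no data share the same 280 days. Profile review would catch some errors.

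All of this limits reach, and it stands. It does not make the rule right. Steps 1 and 2 use the same floor and still take the latest record, with the stated aim of avoiding one from an earlier pregnancy; Step 5 has no such safeguard. Profile review accepts a plausible date when the start is inferred, and a 245-day live birth can look plausible. No sensitivity analysis is planned.

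A reader might infer that any record of an earlier pregnancy within 301 days is admitted; the floor contradicts that. A reader might also infer a one-way bias that creates false recurrence of preterm birth. The stillbirth row of Table 4 gives shifts in both directions, and no recurrence analysis is planned.

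**Conclusion.** The point holds in a limited form. As written, Step 5 can let a PREM record that cannot belong to the delivery override an FT code made at that delivery.

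For an LB or DELIV dated by Step 5, the start is then up to 35 days late against full term or no data. The full amount arises only if any prior birth is at least 308 days earlier and no early PCONF, AGP or OTEST record corrects it. For SB the shift reaches 84 days later, or 84 or 89 days earlier.

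This assumes that the retry count is Table 2's last column and that late-coded or unlinked term records occur in mothers' data. The Protocol gives no frequency for such records, so the effect on the distribution of terms cannot be estimated. The severity is moderate: a cheap correction to a stated rule, not a defect that undermines the study.

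**What to change.** - **Step 5 item 1:** accept only term records dated near the delivery, from a short interval before the outcome date to 30 days after it. Two weeks before is one illustration; the Protocol gives no basis for an exact figure, so the sponsor should choose it from the timing of term records in the data. At minimum, discard any term record dated before the start that it would imply. That removes the 56-day span for LB and DELIV and the 105-day span for SB, but leaves other early records in.
- **Step 5 item 2:** when categories conflict, use the record nearest the outcome date and keep PREM, POSTT, FT as the order for ties only.
- **Wording:** state that the retry count is Table 2's last column, if it is.

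The cost is two lines of text and code, best made before programming because one program runs on all four databases. The downside is that some true term codes entered well before delivery would be lost and those births would take the no-data estimate. For a true preterm LB or DELIV that is 280 instead of 245 days, a start 35 days earlier; for a preterm SB nothing changes, since both values are 196. Counting the records dropped under the chosen window would show how large this loss is.

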## OVERVIEW OF STUDY DESIGN

### Study Design

This study follows a retrospective cohort design. 7 pregnancy episode outcome cohorts will be created and characterized from women with any pregnancy markers or outcomes:

- Live birth (at least one)
- Stillbirth
- Delivery-Live birth or stillbirth
- Trophoblastic Disease
- Ectopic pregnancy
- Induced abortion
- Spontaneous abortion

Women are allowed multiple pregnancy episodes and the unit of analysis will be the pregnancy episode. Valid pregnancy outcomes for each patient will be chosen using an algorithm that utilizes an outcome assessment hierarchy, i.e. live births are assessed for validity first for each patient, any that are too close to another live birth are discarded. Still births for the same patient are then assessed to see if they are too close to all prior assessed live births and any other valid still births etc. Start dates will be assigned using pregnancy markers in a hierarchical fashion also (last menstrual period date records considered as start of pregnancy first, next considered are gestational age estimate records, etc.) See page 12 for a full description of the algorithm.

In medical practices, pregnancy episodes traditionally begin with the last menstrual period date and end with the birth outcome date as defined by the algorithm. The first trimester is defined as week 1-13, 2^nd^ trimester week 14-26 and 3^rd^ trimester week 27-40. For our episodes, the first two weeks of the first trimester will be defined as a pre-exposure period as conception most likely does not happen prior to this time.

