**Pregnancy Episode Start Date Calculation**

To calculate pregnancy episode start date possible start dates will be assigned in the following hierarchy (final start date chosen will be first one assigned in hierarchy):

**Step 1:** LMP (last menstrual period) date as start of pregnancy episode:

1. If LMP records exists between (larger of maximum term allowed subtracted from outcome date or prior outcome date plus retry count) and minimum term allowed subtracted from outcome date then LMP becomes the pregnancy start date
2. If there are more than one LMP records in the live birth window, use the latest so as not to grab a LMP record from an earlier pregnancy episode
3. ~50% of CPRD live births will have an LMP value (median pregnancy length 280 days using LMP date as start of episode); no US claims live births will

**Step 2:** GEST (gestational age in weeks) date as start of pregnancy episode:

1. In CPRD, for GEST record use string_as_value from observation table or in CPRD or US CLAIMS use gest_value from pregnancy concept file, whichever is present. Only use GEST values between 0 and 42 weeks.
2. If GEST record date-(GEST value*7) +1 exists between (larger of maximum term allowed subtracted from outcome date or prior outcome date plus retry count) and minimum term allowed subtracted from outcome date then GEST record date-(GEST value*7) +1 becomes the pregnancy start date.
3. If there are more than one GEST records in the allowed time window, use the latest so as not to grab a GEST record from an earlier episode
4. ~28% of CPRD live births will have a GEST value and not a LMP value with a median pregnancy length 279 days (in CPRD GEST codes are used for any outcome in the additional file); 1.4% of Optum live births will have a GEST value with a median pregnancy length 230 days (in OPTUM GEST codes are used primarily to record a premature birth)

**Step 3:** NULS (nuchal ultrasound) date as start of pregnancy episode:

1. If NULS date-89 exists between (larger of maximum term allowed subtracted from outcome date or prior outcome date plus retry count) and minimum term allowed subtracted from outcome date then NULS date-89 becomes the pregnancy start date.
2. If there are more than one NULS records in the allowed time window, use the first so as to use the NULS date that is most likely the recommended date in clinical guidelines rather than a repeat test.

**Step 4:** AFP (alpha fetoprotein test) date as start of pregnancy episode:

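### Step 6 item 2 replaces the hierarchy's start date, even a recorded LMP, with the raw date of an earlier marker, against the stated rule and the LMP-based definition of start

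*Protocol*

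**What the plan says.** All places are in the Protocol.

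- Pregnancy Episode Start Date Calculation, opening sentence: "final start date chosen will be first one assigned in hierarchy".
- Step 1 item 1, for an LMP record inside the window: "minimum term allowed subtracted from outcome date then LMP becomes the pregnancy start date". With several LMP records, item 2 says to "use the latest so as not to grab a LMP record from an earlier pregnancy episode". Step 2 gives the same reason for taking the latest GEST record.
- Steps 3 and 4 subtract 89 days from the nuchal ultrasound date and 123 days from the AFP date.
- Step 6 item 1: "Choose the best pregnancy start date (first one assigned in steps 1-5").
- Step 6 item 2: if a PCONF, AGP or OTEST record in the window precedes the date "as calculated in the prior 5 steps then the first found PCONF, AGP or OTEST becomes pregnancy start date".
- Study Design summarises the order as "last menstrual period date records considered as start of pregnancy first, next considered are gestational age estimate records". It says that "pregnancy episodes traditionally begin with the last menstrual period date and end with the birth outcome date as defined by the algorithm", and that "the first two weeks of the first trimester will be defined as a pre-exposure period as conception most likely does not happen prior to this".

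**The concern.** The section gives two rules for the final start date. Under the opening sentence and Step 6 item 1, an LMP record in the window settles the matter. Under Step 6 item 2, any earlier confirmation, visit or test in the window displaces it. A programmer can code Step 6 as written, but the result is not the hierarchy that the text describes.

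The substituted date is also of the wrong kind. Study Design counts from the LMP and treats the first two weeks as before conception. Step 6 item 2 can make the day of a pregnancy confirmation day 1, so that the fortnight after a confirmed pregnancy is labelled pre-exposure.

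Start date is half of the primary objective and one of the three proportions to be validated. The protocol expects an LMP for about 50% of CPRD live births and a GEST value without LMP for about another 28%. These recorded dates head its hierarchy, and nothing protects them from the override.

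**Working it through.** **1. The two rules on one case.** Take a CPRD live birth with an LMP record 280 days before birth and an antenatal visit record 295 days before birth. Both lie in the window of 161 to 301 days. The opening sentence and Step 6 item 1 give a start at 280 days. Step 6 item 2 gives 295 days.

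**2. Can the marker date be the start?** There are two possibilities.
- The record belongs to this pregnancy. A confirmation or antenatal visit comes after the LMP, so the start is earlier than the record.
- The record belongs to something else. Then it carries no information on this start.

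In neither case is the marker's own date the start. This is firmest for PCONF and AGP. OTEST is a non-specific category, where an unrelated record is the likelier fault.

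**3. Offsets elsewhere.** Table 3 uses 12.65 and 17.5 weeks. 12.65 × 7 = 88.55, rounded up to 89; 17.5 × 7 = 122.5, rounded up to 123. Both reproduce Steps 3 and 4. Step 6 item 2 subtracts 0.

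**4. Largest shift.** Let M be the maximum term (Table 2) and L the length implied by the date from Steps 1-5 (Table 4, or a stated median). With no prior outcome cutting the window, the largest backward shift is S = M − L.

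**5. Which override records could belong to the pregnancy?** Let d be the days from LMP to the marker. A record m days before the outcome, with L < m ≤ M, fits only if m + d ≤ M. The number of whole days that fit is max(0, S − d). The protocol gives no value for d, so it is an assumption. I show 14 (the pre-exposure period in Study Design) and 28 (the spontaneous-abortion minimum term in Table 2, used only as an illustration).

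| Start date before override | M | L | S | Days that fit, d = 14 | Days that fit, d = 28 |
|---|---|---|---|---|---|
| LB, LMP median or Table 4 full term/no data | 301 | 280 | 21 | 7 | 0 |
| LB preterm | 301 | 245 | 56 | 42 | 28 |
| SB preterm/no data | 301 | 196 | 105 | 91 | 77 |
| AB | 168 | 70 | 98 | 84 | 70 |
| SA | 133 | 70 | 63 | 49 | 35 |
| TRO | 112 | 56 | 56 | 42 | 28 |
| ECT | 84 | 56 | 28 | 14 | 0 |

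For the 280-day live birth, override records lie at 281 to 301 days. Since 281 + 20 = 301, any d above 20 puts every such record past the maximum. With d = 14, records at 281-287 fit and those at 288-301 do not.

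For live births at the other stated medians, S is 301 − 279 = 22 (CPRD GEST), 301 − 230 = 71 (Optum GEST), 301 − 279 = 22 (nuchal ultrasound) and 301 − 276.5 = 24.5 (AFP).

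These are counts of possible calendar days, not shares of records. The protocol does not say how often the override fires.

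**The case against.** The best defence is that Step 6 item 2 is a deliberate plausibility check: a pregnancy should not start after its own antenatal care. Much of this stands.

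- **Direction.** A reader might infer that the override always makes episodes too long. The documents do not support this. A genuine marker moves the start the right way, though not far enough, so the episode is still too short. Only an unrelated marker lengthens it wrongly.
- **Deletion.** A reader might also infer that more episodes would be removed under Exclusion Criteria for starting before observation. Nothing supports this, because the new start is itself the date of a recorded event.
- **Impossible records.** It is tempting to say that no override record can belong to the pregnancy. That holds for the 280-day live birth only if the offset exceeds 20 days. For a 196-day stillbirth estimate, most of the override range is plausible even at 28 days (77 of 105 days).
- **Safeguards.** The window stops at the maximum term and at prior outcome plus retry count. Clinical personnel will judge start dates in CPRD and Optum samples. For live births, no LMP is expected in US claims, so LMP replacement there concerns CPRD only.
- **Study Design.** Its sentence on the order is a summary that refers to the full description. The conflict rests on the calculation section itself.

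Three things remain. The prior-outcome bound protects only against earlier pregnancies whose outcome was captured, and Study Limitations concedes that early miscarriages may be missed. Taking the first record reverses the safeguard of Steps 1 and 2. Steps 3 and 4 also take the first record, but to avoid repeat tests, and they subtract an offset. Finally, no sensitivity analysis is planned that would isolate the override's effect.

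**Conclusion.** The point holds, and should be fixed. Step 6 item 2 contradicts the section's opening sentence and Step 6 item 1. It assigns a date that is not the LMP-based start, whether or not the marker belongs to the pregnancy.

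The size is bounded: at most 21 days for a live birth at 280 days, which is 3 of the 13 first-trimester weeks, and up to 105 days for a stillbirth without term data. These are ceilings and assume that no prior outcome shortens the window. The share of episodes affected cannot be derived from the protocol. Together with the window limits and the planned profile review, that is why this is not rated as a must-fix.

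The contradiction and the missing offset need no assumption about d. Only the statement about which markers can fit depends on it.

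**What to change.** 1. Exempt dates from Steps 1 and 2 (LMP and GEST) from Step 6 item 2.
2. Reword the opening sentence of the section so that it agrees with Step 6.
3. For dates from Steps 3-5, do not use the raw marker date as day 1. State an offset. Ignore a marker that cannot fit within the maximum term once the offset is added to its distance from the outcome. Otherwise set the start to the marker date minus the offset.
4. Report the number of overridden or conflicting episodes by outcome and database.

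Reducing the override to a mere flag on Step 5 dates would go too far. A stillbirth dated at 196 days, with an antenatal visit 260 days before the outcome, would keep a start 260 − 196 = 64 days after documented care, although that visit fits within 301 days at either offset shown.

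The cost is a few sentences, a small code change and one count table, best made before the profiles are drawn for review. There are two downsides. A wrongly recorded LMP or GEST date stays uncorrected, although the conflict count makes it visible. The offset is an assumption that must be stated.
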